### Intervention

#### Moxibustion treatment

Moxibustion treatment will be performed by DKMs who are certified by the Korean Ministry of Health and Welfare. They will have at least 2 years of clinical experience and will have received more than 6 years of oriental medicine college education. The treatment will be performed under the supervision of professors who specialise in acupuncture and moxibustion. All treatment regimens and outcome assessment methods will be standardised between the 4 centres, and basic information about this study and the monitoring process will be disseminated through workshops before the beginning of the study. This study is designed to evaluate moxibustion treatment as it is used in

normal practice. The practitioner will therefore be allowed to maintain a patient-practitioner relationship similar to a normal clinical situation. There will be no restrictions in the careful observation and questioning of participants.

In the moxibustion group, 3 moxibustion sessions per week will be performed during a 4-week period for a total of 12 sessions. The treatment will be conducted after sterilising the skin surface at the acupuncture points with the participant lying in a supine position at a room temperature of 22°C to 28°C. After the top of the moxibustion is sufficiently combusted without attachment to the points for approximately 5 to 10 seconds, the moxibustion will be attached at each point. When a participant believes that their heat tolerance has reached its maximum, the practitioners will place a new moxibustion at the same point. However, to prevent burns, the attached point can be changed to within a 1 cm diameter according to the discretion of the practitioners. A total of 3 moxibustions will be attached at each point at every visit. We will use smokeless indirect moxibustions made of mugwort with a paper cylinder (Manina, Haitnim Co., Korea) (Figure 2). This moxibustion has an adhesive on the bottom that can be used to attach it to the skin, and its effect lasts approximately 5 to 10 minutes. The expected total time of each treatment session will be 20 to 30 minutes. The treatment points were selected in a consensus process by professors and researchers who have an acupuncture and moxibustion specialist license in Korea based on a text book [24], literature reviews [12,14,25],

and the points used in our previous pilot study. The moxibustion group will receive moxibustion treatment on the affected knee(s) at 6 standard acupuncture points (ST36, ST35, ST34, SP9, Ex-LE04, and SP10) plus up to 2 points of 'ashi', if needed, according to the determination of the practitioners (Figure 3). The moxibustion group will also receive the care provided to the usual care group.

Usual care

According to pragmatic design, the control group will not use a placebo procedure. Both the moxibustion and usual care groups will be allowed to use any type of treatment desired, including surgery, conventional medication, physical treatment, acupuncture, herbal medicine, over-the-counter drugs, and other active treatments. However, the participants will be asked to inform the research investigators of any new treatments performed after entry into the trial. Educational materials explaining KOA and self-exercise will be provided to each group. The participants in both groups will perform self-exercise, which consists of 1) stretching the hamstrings, biceps femoris, and ankles on both sides 3 times per day and 2) muscle exercises for the hamstrings and biceps femoris (including isometric and isotonic exercises) on both sides according to the disease status during the trial period.

Outcome

Primary outcome measurement

The primary outcome with respect to the effectiveness on KOA will be the mean change in the global scale value of the Western Ontario and McMaster Osteoarthritis Index (WOMAC) from baseline to 5 weeks. The WOMAC is

[figure not shown]

**Figure 2 Moxibustion device.** A photograph of the moxibustion device that will be used in this trial. This moxibustion device is a sticker-type disposable moxa, which functions for 5–10 minutes and is used for local acupuncture points. M: the upper part of the carbonised mugwort, A: adhesive sticker, H: height (2.1 cm), D: distance (1.9 cm).

[figure not shown]

**Figure 3 Acupuncture points of treatment.** The right knee will be treated at 6 standard acupuncture points (ST36, ST35, ST34, SP9, Ex-LE04, and SP10). The left knee will be treated with an additional point of 'ashi', which is located between ST35 and Ex-LE04. A: additional points of 'ashi' according to the determination of the practitioner. A Written consent for the picture was obtained from the pictured subject. Photograph by [name].

one of the most widely used instruments and is composed of 24 questions to assess disability related to osteoarthritis. It includes 3 subscales to measure pain (5 questions), stiffness (2 questions), and physical function (17 questions) in KOA, and higher scores indicate more severe impairment [26,27]. There is a Korean version of the WOMAC (K-WOMAC), and Bae *et al.* confirmed its reliability, validity, and responsiveness [28]. We will therefore assess participants at the second visit (before starting moxibustion treatment) and at 5 weeks and 13 weeks from baseline using the K-WOMAC.

### Secondary outcome measurements

Secondary outcomes include the mean changes in the WOMAC subscales (pain, stiffness, and function) at 5 and 13 weeks from baseline. As such, we will investigate which subscales affect the global scale value of the WOMAC, which is the primary outcome measurement.

Health-related quality of life (HRQL) will be assessed by the Short-Form 36v2 Health Survey (SF-36) at 5 and 13 weeks from baseline. The SF-36 is used to measure the general health status and quality of life of patients and non-patients. It comprises a total of 36 questions in 8 categories, and higher scores indicate a better level of function. Han *et al.* developed a Korean version of the SF-36 and assessed its reliability and validity for use in health-related quality of life measurements for elderly Korean patients [29].

Depression will be assessed by a mean change in Beck Depression Inventory (BDI) scores at 5 and 13 weeks from baseline. The BDI, developed by Beck AT in 1967, is a 21-question multiple-choice questionnaire that is one of the most widely used scales for measuring the severity of depression. It is composed of items related to the depression symptoms of hopelessness and irritability, cognition (such as guilt and feelings of being punished), and physical symptoms (such as fatigue and weight loss); higher total scores indicate more severe depressive symptoms [30].

To assess physical activity, a physical performance test will be performed at 5 and 13 weeks from baseline. The physical performance test is composed of the timed stand, standing balance, and 6-minute walk tests. 1) The timed stand test evaluates lower extremity muscle power by measuring the time required to complete 10 full stands from a sitting position. 2) The standing balance test assesses balance in particular positions, such as tandem, semi-tandem, side-by side, and one-legged stands. 3) The 6-minute walk test measures the distance walked at the greatest speed possible within 6 minutes to assess the functional exercise capacity of patients [31].

Global knee pain will be assessed using the patient global assessment and numerical rating scale (NRS). The patient global assessment score is a self-reported 5-point

measurement used to evaluate overall improvement after treatment. Participants individually evaluate their improvement from baseline by selecting one of 5 options (much improved, minimally improved, no change, minimally worse, or much worse) at 5 and 13 weeks from baseline. The pain NRS (0 = no pain and 10 = worst possible pain) is a standard instrument in chronic pain studies that is used to measure pain intensity [32]. We will evaluate the mean change in the NRS within 7 days of the study visits at 5 and 13 weeks from baseline.

The treatment expectancy of participants will be evaluated by the Treatment Expectancy Questionnaire (1 = not at all, 5 = somewhat and 9 = very much), which has been transformed and translated into Korean from the "Credibility and Expectancy Questionnaire" [33]. Participants will be asked "How much do you feel moxibustion therapy will help to reduce your symptoms?" at the first visit.

A blood sample will be obtained at baseline and 5 weeks from baseline to measure the C-reactive protein (CRP) levels and the erythrocyte sedimentation rate (ESR). We will therefore evaluate inflammation and tissue damage after moxibustion treatment. The detailed outcome measurement time points are provided in Table 1.

### Sample size

We calculated the sample size according to our previous pilot study. A 2-sided 5% significance level and 80% power were considered to detect a mean difference in the WOMAC of -6.65 with a standard deviation (SD) of 15.4. Approximately 84 participants in each group were calculated to be required. Assuming a dropout rate of 20%, the sample size will be  $n = 106$  for each group (total  $n = 212$ ). A total of 32 participants will be assigned at the Korea Institute of Oriental Medicine (Daejeon University Hospital), and the remaining 180 participants will be equally assigned at the other 3 study hospitals. To recruit this number of participants, a 6-month study period is anticipated based on our pilot study.

### Statistical analysis

The statistical analysis will be performed on the intention-to-treat basis with a 95% confidence interval using SAS (Version 9.1.3; SAS institute Inc., Cary, NC, USA). Missing data will be replaced according to the principle of the last observation carried forward (LOCF) method. The null hypothesis is that there will be no difference in the change in the primary outcome between the moxibustion group and the usual care group after 5 weeks of treatment. The baseline characteristics will be shown as the mean  $\pm$  SD for continuous data (e.g., age and duration of disease) and  $n$  (%) for categorical data (e.g., gender and Kellgren/Lawrence Scale).

To analyse the baseline characteristics, we will perform a 2-sample *t*-test or a Wilcoxon rank sum test for

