| Patient Global Assessment          |        |   | • |   |   |   |   |   |   |   |    |    |    |    | •  | •  |
| Safety Assessment                  |        |   | • | ○ | ○ | ○ | ○ | ○ | ○ | ○ | ○  | ○  | ○  | ○  | •  | •  |

S: Screening Period, T: Treatment Period, F: Follow-up Period, K-WOMAC: Korean Western Ontario and McMaster Osteoarthritis Index, •: Both the moxibustion group and the usual care group, ○: Only the moxibustion group.

continuous data and a chi-squared test or Fisher's exact test for categorical data, according to whether the data are normally distributed. An analysis of covariance (ANCOVA) will be performed for the primary endpoint (global scale value of WOMAC) and secondary endpoints (WOMAC subscales (pain, stiffness, and function), HRQL, depression, physical activity, and patient global assessment) at 5 weeks and 13 weeks from baseline. The ANCOVA model will include group as a fixed effect and baseline measurements and centres as covariates. The mean difference from baseline values to the end of treatment in each group will be examined using a paired *t*-test or a Wilcoxon signed rank test. To identify a trend, we will also perform a repeated measures analysis of variance.

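### With no K-WOMAC between baseline and week 5, LOCF scores every missing primary outcome as zero change, which dilutes a true effect and can bias the comparison either way if dropout differs by arm

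*Protocol*

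**What the plan says.** The Protocol's Statistical analysis section sets an intention-to-treat analysis and then states: "Missing data will be replaced according to the principle of the last observation carried forward (LOCF) method". It names no other method.

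The primary outcome (Primary outcome measurement) is the "mean change in the global scale value of the Western Ontario and McMaster Osteoarthritis Index (WOMAC) from baseline to 5 weeks". The instrument is given "at the second visit (before starting moxibustion treatment) and at 5 weeks and 13 weeks from baseline using the K-WOMAC". Table 1 agrees: K-WOMAC is marked at visits 2, 14 and 15 only.

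The primary and secondary endpoints are compared at weeks 5 and 13 by ANCOVA with group, baseline value and centre. The section adds: "To identify a trend, we will also perform a repeated measures analysis of variance".

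The Sample size section takes about 84 participants per group and raises this to 106 for losses ("Assuming a dropout rate of 20" per cent).

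**The concern.** LOCF needs an earlier post-baseline value to carry forward. For the week-5 endpoint there is none, so the rule assigns the baseline score and the change becomes exactly zero. The ANCOVA then treats that zero as a measurement.

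Zero is a poor guess here. Both arms receive education and self-exercise and may use any other treatment, so some improvement in both is plausible. The error cancels between arms only if there is no true effect and dropout is equal.

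Equal dropout cannot be taken for granted. Participants know their allocation (Randomisation and allocation concealment). Table 1 gives the moxibustion arm twelve treatment visits, while usual care has no study visit between visit 2 and visit 14. What is at stake is the size of the primary estimate and, if dropout is unequal, its false-positive rate.

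**Working it through.** **Inputs from the Protocol (Sample size).** Difference -6.65, SD 15.4, two-sided 5%, 80% power, about 84 per group, 20% dropout, 106 per group. Negative values mean improvement.

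**Assumptions not in the Protocol.** The SD of 15.4 is that of the change score. Dropout is random within arm. The mean change per arm, the split of dropout by arm, the timing of dropout and the true week-13 effect are all assumed, and ranges are shown.

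**1. The plan's own figure.** n = 2 × [(1.960 + 0.842) × 15.4 / 6.65]² = 84.2 per group. Dividing by 0.8 gives 105.2 from 84.2, or 106.25 from 85. The stated 84 and 106 reproduce to rounding.

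**2. Participants affected.** 0.20 × 106 = 21.2, so about 21 per arm have a week-5 change set to zero.

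**3. Model.** With dropout d and mean change m in an arm (T moxibustion, C usual care):
- expected LOCF difference = (1 - dT) × mT - (1 - dC) × mC
- variance per arm = (1 - d) × 15.4² + d × (1 - d) × m²
- standard error = √[(varT + varC) / 106]

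**4. Equal 20% dropout.** The difference is 0.8 × (mT - mC). A true -6.65 becomes 0.8 × (-6.65) = -5.32, whatever the usual-care change. A true 0 stays 0, and type I error stays at 5%.

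**5. No true effect, unequal dropout.** Take a change of -10 in both arms, with 10% moxibustion and 30% usual-care dropout.
- Difference: 0.9 × (-10) - 0.7 × (-10) = -2.0, which is 2.0 / 6.65 = 30% of the target.
- Variances: 0.9 × 237.16 + 0.09 × 100 = 222.4, and 0.7 × 237.16 + 0.21 × 100 = 187.0.
- SE: √(409.5 / 106) = 1.97.
- Two-sided rejection rate: 17.4%.

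| Change in both arms | 10%/30%: false difference, type I error | 15%/25%: false difference, type I error |
|---|---|---|
| -5 | -1.0, 8.2% | -0.5, 5.8% |
| -10 | -2.0, 17.4% | -1.0, 8.0% |
| -15 | -3.0, 30.9% | -1.5, 11.3% |

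Swapping the arms reverses the sign and leaves the error rate unchanged. These are unadjusted tests. A simulated ANCOVA (assumed baseline SD 16, slope of change on baseline -0.45) gave about 21% for the -10, 10%/30% case, against about 5% on observed data.

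**6. True effect -6.65, usual-care change -10 (so mT = -16.65).**

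| Dropout, moxibustion/usual care | Arithmetic | LOCF estimate |
|---|---|---|
| 30%/10% | -11.655 + 9 | about -2.65 |
| 25%/15% | -12.4875 + 8.5 | about -3.99 |
| 15%/25% | -14.1525 + 7.5 | about -6.65 (errors happen to cancel) |
| 10%/30% | -14.985 + 7 | about -7.98 |

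**7. Week 13.** Participants lost after week 5 carry their week-5 score; those lost earlier carry baseline. Suppose the benefit is 6.65 points at week 5 and 3 at week 13, with 20% lost in total in each arm.
- All lost after week 5: 0.8 × 3 + 0.2 × 6.65 = 3.73.
- Half before, half after: 0.8 × 3 + 0.1 × 6.65 + 0.1 × 0 = 3.07.
- All lost before week 5: 0.8 × 3 = 2.40.

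If the true week-13 effect is 0, the three results are 1.33, 0.67 and 0.

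**8. Power, equal 20% dropout, true effect -6.65.** The unadjusted test with LOCF has 79.6%, 77.7%, 74.3% or 69.6% power for a usual-care change of 0, -5, -10 or -15. The planned analysis is ANCOVA, and its simulated power with LOCF is about 80% to 87% for a usual-care change between -10 and 0, against 88% to 89% on observed data.

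**The case against.** The strongest reply is that LOCF is often conservative and that the alarming figures need inputs the Protocol does not give. Much of this stands. The plan states a single 20% dropout rate with no split by arm and gives no mean change per arm. With equal dropout the false-positive rate is untouched and a real effect is merely diluted. A mild imbalance with modest improvement moves type I error only to 5.8%. The direction of imbalance is also open: usual care has fewer contacts, but moxibustion has twelve sessions and known blisters and burns (Adverse events).

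Two stronger readings are tempting and not supported:

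- **LOCF favours a lasting benefit at week 13.** This holds only if most losses come after week 5. Participants lost earlier carry baseline, which pulls the other way, and the Protocol does not give the timing of dropout.
- **The trial is underpowered because the sample size counts completers while LOCF keeps dropouts in at zero.** The mismatch exists, but the lower power figures belong to an unadjusted test. The planned ANCOVA stays near or above 80% in the simulations cited, which themselves rest on assumed inputs.

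It is also fair to say that the alternatives look unbiased here because dropout was taken as random within arm. If open-label dropout depends on unobserved outcomes, they can be biased too.

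The reply does not rescue LOCF as the primary method. Its error depends on who leaves which arm, so it cannot be relied on to be conservative. Nor is this a matter left to a later plan: the Protocol names the method outright.

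**Conclusion.** The concern holds for the primary endpoint. It follows from the assessment schedule and the fixed rule that each missing week-5 score is analysed as zero change, about 21 per arm at the planned dropout.

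The dilution from -6.65 to -5.32 needs only equal 20% dropout at random within arm. The false 2.0-point difference with about 17% type I error, and the range from -2.65 to -7.98 around a true -6.65, also need the assumed 10-point improvement and the assumed dropout splits. They show what can happen; they do not predict it. There is no bias if dropout is equal and there is no true effect.

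At week 13 bias is possible in either direction. No shortfall from the stated power is established for the planned ANCOVA.

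**What to change.** In the Protocol's Statistical analysis section, replace LOCF as the primary method with one of the following:

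- a likelihood-based longitudinal model of K-WOMAC at baseline, week 5 and week 13, with group-by-time and centre terms and the week-5 group contrast as the primary test; or
- multiple imputation by arm, followed by the ANCOVA already stated.

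Keep LOCF at most as a sensitivity analysis.

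The cost is rewording and some extra programming; no added participants, visits or data are needed. Both options rely on a missing-at-random assumption, which a delta-adjusted sensitivity analysis by arm can probe.

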**Table 1 Schedule for treatment and outcome measurements**

|                                    | Period | S |   |   |   |   |   |   | T |   |    |    |    |    |    | F  |
|------------------------------------|--------|---|---|---|---|---|---|---|---|---|----|----|----|----|----|----|
|                                    | Visit  | 1 | 2 | 3 | 4 | 5 | 6 | 7 | 8 | 9 | 10 | 11 | 12 | 13 | 14 | 15 |
|                                    | Week   | 1 | 1 | 1 | 1 | 2 | 2 | 2 | 3 | 3 | 3  | 4  | 4  | 4  | 5  | 13 |
| Informed Consent                   |        | • |   |   |   |   |   |   |   |   |    |    |    |    |    |    |
| Demographic Characteristics        |        | • |   |   |   |   |   |   |   |   |    |    |    |    |    |    |
| Medical History                    |        | • |   |   |   |   |   |   |   |   |    |    |    |    |    |    |
| Knee X-Ray                         |        | • |   |   |   |   |   |   |   |   |    |    |    |    |    |    |
| Inclusion/Exclusion Criteria       |        | • |   |   |   |   |   |   |   |   |    |    |    |    |    |    |
| Conformity Assessment              |        | • |   |   |   |   |   |   |   |   |    |    |    |    |    |    |
| Treatment Expectancy Questionnaire |        | • |   |   |   |   |   |   |   |   |    |    |    |    |    |    |
| Blood Test                         |        | • |   |   |   |   |   |   |   |   |    |    |    |    | •  |    |
| Vital Signs                        |        | • | • | ○ | ○ | ○ | ○ | ○ | ○ | ○ | ○  | ○  | ○  | ○  | •  | •  |
| Change in Medical History          |        |   | • | ○ | ○ | ○ | ○ | ○ | ○ | ○ | ○  | ○  | ○  | ○  | •  | •  |
| Random Allocation                  |        | • |   |   |   |   |   |   |   |   |    |    |    |    |    |    |
| Moxibustion Treatment              |        |   | ○ | ○ | ○ | ○ | ○ | ○ | ○ | ○ | ○  | ○  | ○  | ○  |    |    |
| K-WOMAC                            |        |   | • |   |   |   |   |   |   |   |    |    |    |    | •  | •  |
| Beck Depression Inventory          |        |   | • |   |   |   |   |   |   |   |    |    |    |    | •  | •  |
| The Short-Form 36v2 Health Survey  |        |   | • |   |   |   |   |   |   |   |    |    |    |    | •  | •  |
| Pain Numerical Rating Scale        |        | • | • |   |   |   |   |   |   |   |    |    |    |    | •  | •  |
| Physical Function Test             |        |   | • |   |   |   |   |   |   |   |    |    |    |    | •  | •  |
| Patient Global Assessment          |        |   | • |   |   |   |   |   |   |   |    |    |    |    | •  | •  |
| Safety Assessment                  |        |   | • | ○ | ○ | ○ | ○ | ○ | ○ | ○ | ○  | ○  | ○  | ○  | •  | •  |

S: Screening Period, T: Treatment Period, F: Follow-up Period, K-WOMAC: Korean Western Ontario and McMaster Osteoarthritis Index, •: Both the moxibustion group and the usual care group, ○: Only the moxibustion group.

continuous data and a chi-squared test or Fisher's exact test for categorical data, according to whether the data are normally distributed. An analysis of covariance (ANCOVA) will be performed for the primary endpoint (global scale value of WOMAC) and secondary endpoints (WOMAC subscales (pain, stiffness, and function), HRQL, depression, physical activity, and patient global assessment) at 5 weeks and 13 weeks from baseline. The ANCOVA model will include group as a fixed effect and baseline measurements and centres as covariates. The mean difference from baseline values to the end of treatment in each group will be examined using a paired *t*-test or a Wilcoxon signed rank test. To identify a trend, we will also perform a repeated measures analysis of variance.

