## Abstract

**Background:** The treatment of knee osteoarthritis, which is a major cause of disability among the elderly, is typically selected from multidisciplinary options, including complementary and alternative medicine. Moxibustion has been used in the treatment of knee osteoarthritis in Korea to reduce pain and improve physical activity. However, there is no sufficient evidence of its effectiveness, and it cannot therefore be widely recommended for treating knee osteoarthritis. We designed a randomised controlled clinical trial to evaluate the effectiveness, safety, cost-effectiveness, and qualitative characteristics of moxibustion treatment of knee osteoarthritis compared to usual care.

**Methods/designs:** This is a protocol for a multicentre, pragmatic, randomised, assessor-blinded, controlled, parallel-group study. A total of 212 participants will be assigned to the moxibustion group (n = 106) and the usual care group (n = 106) at 4 clinical research centres. The participants assigned to the moxibustion group will receive moxibustion treatment of the affected knee(s) at 6 standard acupuncture points (ST36, ST35, ST34, SP9, Ex-LE04, and SP10) 3 times per week for 4 weeks (a total of 12 sessions). Participants in the usual care group will not receive moxibustion treatment during the study period. Follow-up will be performed on the 5th and 13th weeks after random allocation. Both groups will be allowed to use any type of treatment, including surgery, conventional medication, physical treatment, acupuncture, herbal medicine, over-the-counter drugs, and other active treatments. Educational material that explains knee osteoarthritis, the current management options, and self-exercise will be provided to each group. The global scale of the Korean Western Ontario and McMaster Osteoarthritis Index (K-WOMAC) will be the primary outcome measurement used in this study. Other subscales (pain, stiffness, and function) of the K-WOMAC, the Short-Form 36v2 Health Survey, the Beck Depression Inventory, the Physical Function test, Patient Global Assessment, and the Pain Numerical Rating Scale will be used as outcome variables to evaluate the effectiveness of moxibustion. Safety will be assessed at every visit. In addition, an economic evaluation and a qualitative study will be conducted as a mixed-methods approach.

**Discussion:** This trial may contribute to developing evidence for the effectiveness and safety of moxibustion for treating knee osteoarthritis.

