## Methods/design

### Objective

The aims of this study are as follows: (1) to assess the effectiveness of moxibustion treatment for treating KOA on the occurrence of pain, function, depression, quality of life, and adverse events compared to usual care and (2) to assess the cost-effectiveness and cost-utility of moxibustion in addition to usual care in the treatment of KOA patients and explore how KOA patients experience moxibustion in Korea.

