#### **Adverse events**

All unexpected and unintended responses that are not necessarily related to moxibustion treatment will be reported by the participants and practitioners at every visit. The adverse events known to occur following moxibustion treatment include blisters, redness, itching, burns, and respiratory symptoms. To avoid potential adverse events, the treatment day will be modulated within 3 days if the practitioner judges that the participant is not suitable for moxibustion treatment or the participant indicates moderate fatigue or an abnormal health condition.

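### Safety is assessed at 13 post-baseline visits with moxibustion but only 2 in usual care, so a crude between-group comparison of non-specific adverse events is likely to be biased against moxibustion

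*Protocol*

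**What the plan says.** The Objective section makes safety comparative. The first aim covers, among other things, "quality of life, and adverse events compared to usual care".

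The Adverse events section says how events are gathered: "All unexpected and unintended responses that are not necessarily related to moxibustion treatment will be reported by the participants and practitioners at every visit". The Abstract agrees: "Safety will be assessed at every visit". The next sentence of the Adverse events section lists reactions already known to follow moxibustion: blisters, redness, itching, burns and respiratory symptoms.

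Table 1 fixes the visits. Its legend gives the filled circle as "Both the moxibustion group and the usual care group, ○: Only the moxibustion group". The row "Safety Assessment" has the filled circle at visits 2, 14 and 15 and the open circle at visits 3 to 13. The row "Change in Medical History" has the same pattern.

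The Usual care section adds that, in both groups, "the participants will be asked to inform the research investigators of any new treatments performed after entry into the trial". It ties this to no visit. The Economic evaluation section collects all cost data by a participant questionnaire at weeks 5 and 13.

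**The concern.** Adverse event counts in two arms are comparable only if each arm has a similar chance of having an event noticed and recorded. Here recording is tied to visits, and the visits differ by arm. During the treatment weeks a moxibustion participant is asked every two or three days, face to face, with a practitioner who may also report. A usual care participant is next asked at week 5 and must recall about four weeks.

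Since events are collected whatever their cause, the tally will include headaches, colds, back pain and other minor complaints that occur in either arm. These short-lived events are the ones most easily lost to recall. A crude comparison would tend to credit moxibustion with an excess that comes from the schedule, and a stated aim of the trial would rest on counts that are not like for like.

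There is also a wording problem in the collection rule. It covers responses that are *unexpected*, although the section goes on to name reactions that are expected. Read literally, the rule leaves out the harms the protocol itself anticipates.

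**Working it through.** **Counts.** The protocol does not total the visits, so there is no stated figure to reproduce. Counting the symbols in the safety row of Table 1:

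- Filled circles (both arms): visits 2, 14, 15 = 3.
- Open circles (moxibustion only): visits 3 to 13 = 11.
- All visits: moxibustion 3 + 11 = 14; usual care 3.
- Visit 2 is the pre-treatment baseline in both arms. After baseline: moxibustion 14 − 1 = 13; usual care 3 − 1 = 2.
- Between visit 2 and visit 14: moxibustion 11; usual care 0.

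As a cross-check, treatment runs over visits 2 to 13, which is 12 visits and matches the 12 planned sessions. From visit 14 (week 5) to visit 15 (week 13) the schedules are identical. The imbalance therefore lies wholly in the weeks up to week 5.

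**Apparent risk ratio.** The protocol gives no event rates and no recall fractions, so what follows is assumption. Let the true risk p be the same in both arms, and let a fraction c of events be captured. The recorded risk is p × c, so

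apparent risk ratio = (p × c_moxibustion) / (p × c_usual care) = c_moxibustion / c_usual care.

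The ratio does not depend on p. With p = 0.20 and c_moxibustion = 0.9, moxibustion records 0.20 × 0.9 = 0.18.

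| Capture in usual care | Recorded risk, usual care | Apparent risk ratio |
|---|---|---|
| 0.5 | 0.20 × 0.5 = 0.10 | 0.18 / 0.10 = 1.80 |
| 0.7 | 0.20 × 0.7 = 0.14 | 0.18 / 0.14 = 1.29 |
| 0.9 | 0.20 × 0.9 = 0.18 | 0.18 / 0.18 = 1.00 |

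**Would it show at this sample size?** Take the planned 106 per arm, complete capture with moxibustion and capture r in usual care, so p1 = p and p2 = p × r. The chance of a nominally significant moxibustion excess at two-sided 5% is approximately

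Φ{ (p1 − p2 − 1.96 × √[2 p̄(1 − p̄)/106]) / √[(p1(1 − p1) + p2(1 − p2))/106] }, with p̄ the mean of p1 and p2.

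For p = 0.20 and r = 0.5: p̄ = 0.15, the two standard errors are 0.0490 and 0.0486, and (0.10 − 0.0961)/0.0486 = 0.08, giving 53%.

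| True risk in both arms | r = 0.9 | r = 0.7 | r = 0.5 |
|---|---|---|---|
| 0.10 | 4% | 12% | 28% |
| 0.20 | 6% | 21% | 53% |
| 0.30 | 7% | 32% | 75% |

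With equal capture the figure in this one direction would be 2.5%. The bias is small if recall is nearly complete and large if half the control events are lost.

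**The case against.** The case on the other side is substantial, and much of it limits the point without removing it.

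- *Contradiction.* A reader might infer that Table 1 contradicts the statements that safety is assessed at every visit. It does not. Usual care participants have no visits 3 to 13, and every visit they attend after screening carries a safety assessment. The statements are consistent; the consequence is unequal ascertainment.
- *Cost data.* A reader might infer that the economic evaluation suffers too. The protocol rules that out: all cost data come from a questionnaire with the same timing in both arms.
- *Co-treatment.* A reader might infer that new treatments are under-recorded in controls, because the "Change in Medical History" row follows the same pattern. That row does not name treatments, and both arms are asked to report new treatments by a route not tied to visits. At most the effect is weak.
- *Skin reactions.* Blisters and burns from moxibustion arise in the treated arm only, so unequal questioning matters little for them. The bias concerns mild, non-specific events; serious events should be less vulnerable to four weeks of recall.
- *Burns undercounted.* A reader might infer that known burns will go unrecorded. The section calls them adverse events and a safety assessment is scheduled at each session, so the authors probably intend to record them. The wording is loose and worth correcting, but the documents do not show that burns would be missed.
- *Analysis plan.* The protocol specifies no test of adverse events, and an unseen SAP may define the safety tables. That stands as to analysis. But the protocol fixes the collection schedule, and no analysis recovers events that were never elicited.
- *Comparator.* More contact with controls would alter the usual care comparator of a pragmatic trial. This is a fair reason not to demand equal visits.

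**Conclusion.** The point holds for between-group comparison of adverse events that can occur in either arm. Post-baseline elicitation is 13 visits against 2, with 11 against 0 before week 5, and the protocol neither describes interim contact with controls nor limits the comparison to shared visits. The likely direction is more recorded events with moxibustion.

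The counts are exact. The size of the bias is not known: the risk ratio of about 1.3 to 1.8 assumes 90% capture at frequent visits and 50% to 70% capture by 4-week recall, and it shrinks to 1.0 if recall does as well as frequent questioning. The calculation shows what could happen; it does not predict a false safety signal.

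The primary K-WOMAC endpoint, measured at visits 2, 14 and 15 in both arms, is unaffected. The matter should be corrected because a named aim depends on it, but it does not threaten the main result.

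**What to change.** 1. Define the between-group adverse event comparison on one identical recall question, put to both arms at visits 14 and 15 and covering the time since the last common visit.
2. Report events recorded at visits 3 to 13 separately, as a descriptive profile of the moxibustion arm, so that no safety information is lost.
3. State that some bias remains. By visit 14 moxibustion participants will have been asked 11 times, which may prime their recall. Equal-frequency contact would deal with this better, but it costs more and changes the comparator.
4. In the Adverse events section, replace the opening of the reporting rule with *All unfavourable and unintended responses, whether expected or not*, so that the known reactions are plainly included.

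The cost is a change of wording, one standard question on the week-5 and week-13 case report forms, and one extra table. The downside is that the between-group comparison uses fewer of the moxibustion arm's records.
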